### Study design

This is a quadruple-blind (participant, intervention provider, investigator and analyst) cluster-randomised placebo-controlled trial.

Twenty-four clusters have been assigned in a 1:1 ratio to one of two trial arms using restricted randomisation^44^:

Intervention (DP and IVM MDA).Control (DP and IVM-placebo MDA).

Restriction variables included population, baseline *P. falciparum* prevalence (qPCR and RDT), vector density, SMC coverage and presence of a health centre. Of 100 000 randomisations, the final randomisation was selected from the approximately 10% satisfying the criteria.

This protocol was developed using SPIRIT reporting guidelines.^45 46^ A timeline is shown in figure 1.

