#### Primary outcome

Trial arms will be compared using a t-test on cluster-level malaria qPCR prevalences. A risk difference, 95% CI and p value will be presented. Analyses adjusting for age groups (<5 years, 5–14 years, 15 years and above), bed net use and the presence of a health centre will be presented for this and all secondary outcomes.

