#### Secondary outcomes

As for the primary outcome, using data from the year 1 survey.Cluster-level incidence rates will be compared using a t-test. If the distribution is markedly skewed, then the natural logarithm of each cluster-level summary will be taken. If some clusters have zero events, then 0.5 events will be added to each cluster. Rate differences, 95% CI and p value will be presented.As for outcome 2, using RDT-confirmed incidence rates from the two annual cohorts of children.As for outcome 3, using qPCR-confirmed incidence rates. Serological analysis described in outcome 5.Cluster-level serological responses to malaria antigens will be presented as both continuous median fluorescent intensity (MFI) data, a proxy for antibody titres, and binary seropositivity prevalence, with a seropositivity threshold of three standard deviations above the mean malaria-naïve MFI responses. MFI will be compared between arms using mixed effect linear regression, with a random effect for cluster. Seropositivity will be compared in the same way as the primary outcome, including analysis by age group. Cluster-level antigen-specific seroconversion rates (SCR) will be generated using serocatalytic models relying on seroprevalence, and age-seroprevalence plots will be generated by fitting data to a reversible catalytic conversion model using maximum likelihood methods. Trial arms’ SCR will be compared using a t-test.^53^As for outcome 5, using the gSG6 antigen and not employing SCR.Cluster-level anopheline parity will be compared between arms using a t-test. Adjustment will be made for species, MDA round, time relative to MDA date, temperature, humidity and rainfall. Parity difference, 95% CI and p value will be presented.The proportion of each species identified, and mosquito densities, will be presented by cluster and arm, and compared using χ^2^ and t-tests. Adjustment will be made for study month and year. Differences, 95% CIs and p values will be presented. If the distribution of densities is markedly skewed, a log transformation will be applied. SR will be compared between arms using a t-test on cluster-level SR with adjustments and covariates as described for parity analysis above. Risk difference, 95% CI and p value will be presented. EIR will be compared with a t-test on cluster level summaries.Species composition and level of resistance will be presented using descriptive statistics. Dose–response curves will be generated for each insecticide and probit regression analysis will be performed on these data using maximum likelihood or least squares methods.The number of alleles associated with antimalarial resistance will be compared over time, before and after MDA. However, appropriate statistical tests will need to be selected depending on the allele sample size before and after MDA.Descriptive statistics will be presented on the number, nature, severity and relatedness of all reported AE, with additional details for serious AE. Cluster-level and age-group data will be presented. Rates will be compared between arms.As for the primary outcome and outcome 5.Cluster-level, arm-level and overall coverage will be presented for each month and year of intervention, and for the trial overall. The denominator for these proportions will be the total number of people recorded on MDA administration records by distributors in each cluster, whether receiving MDA or not. Refusals, exclusions and absences will be presented similarly.Qualitative and quantitative analysis of MDA acceptability, feasibility and access will be outlined in a separate protocol.Cost-effectiveness analysis will be detailed in a separate protocol.

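### Mosquito density and EIR are compared between arms without adjusting for the pre-trial vector density on which the allocation was restricted, at an avoidable cost in precision

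*Protocol article*

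**What the plan says.** Under Study design, the article states: "Twenty-four clusters have been assigned in a 1:1 ratio to one of two trial arms using restricted randomisation". The restriction variables include "vector density, SMC coverage and presence of a health centre", alongside population and baseline parasite prevalence, and "the final randomisation was selected from the approximately 10% satisfying the criteria".

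Under Data analysis plan, Secondary outcomes, item 8, species proportions and "mosquito densities, will be presented by cluster and arm, and compared using" chi-squared and t-tests. The covariates named there are month and year: "Adjustment will be made for study month and year". For the entomological inoculation rate: "EIR will be compared with a t-test on cluster level summaries". No covariate specific to EIR is named.

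Under Data analysis plan, Primary outcome, a general rule says that analyses adjusting for age group, "bed net use and the presence of a health centre will be presented for this and all secondary outcomes".

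Of the restriction variables, only health-centre presence is carried into an analysis. Vector density is not a covariate for any outcome.

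**The concern.** Earlier mosquito abundance in a cluster is a natural predictor of later abundance in that cluster. A value of it was used to restrict the allocation, but the covariates fixed for density and EIR leave it out. Those that are included are weak substitutes. Month and year are largely shared by the arms, because the Intervention and control section has MDA starting in all clusters at once and trapping is timed to the MDA rounds and the peak survey. Human age group, bed net use and a health centre do not record how many mosquitoes a cluster had.

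Two things follow. Predictable between-cluster variance stays in the error term, so intervals are wider than they need be. And because the restriction has already balanced the arms on this variable, a t-test that ignores it charges for variation the design has partly removed, so it rejects too rarely.

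Density and EIR are part of the evidence on whether ivermectin acts through the vector. They rest on 18 clusters in year 1 and 24 in year 2, with traps in one village per cluster and 10 or 15 households. With so few units, a good cluster-level covariate is worth having.

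**Working it through.** **The plan's own power figure.** The only one is for the primary outcome: above 80% with 12 clusters per arm, 200 people per cluster, coefficient of variation 0.46, and 10% against 5%. The standard formula for unmatched clusters gives

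V = 0.10×0.90/200 + 0.05×0.95/200 + 0.46²×(0.10² + 0.05²) = 0.00045 + 0.00024 + 0.00265 = 0.00333.

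Clusters per arm for 80% power = 1 + (1.960 + 0.842)²×0.00333/0.05² = 11.5. Power with 12 is 81.8% by noncentral t on 22 degrees of freedom. The stated figure reproduces. None is given for density or EIR, so what follows starts from assumed powers.

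**Inputs for the precision check.** Number of clusters C: 24 (year 2) or 18 (year 1), from Assessment of outcomes, Secondary. Assumed: two-sided 5% test; starting power 80% or 50%; correlation ρ between the pre-trial value and the trial summary of 0, 0.3, 0.5 or 0.7.

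**Method.** Adjusting for one cluster-level covariate multiplies the residual variance by 1 − ρ² and lowers the degrees of freedom from C − 2 to C − 3. The noncentrality is therefore divided by √(1 − ρ²). With C = 24, 80% power corresponds to a noncentrality of 2.93; at ρ = 0.5 it becomes 2.93/√0.75 = 3.39 on 21 degrees of freedom.

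| ρ | Variance removed | CI width, C = 24 | 80% becomes (C = 24 / 18) | 50% becomes (C = 24 / 18) |
|---|---|---|---|---|
| 0 | 0% | ×1.003 | 79.8% / 79.7% | 49.8% / 49.7% |
| 0.3 | 9% | ×0.96 | 83.4% / 83.2% | 53.6% / 53.4% |
| 0.5 | 25% | ×0.87 | 89.7% / 89.6% | 61.7% / 61.5% |
| 0.7 | 49% | ×0.72 | 97.4% / 97.4% | 78.1% / 77.9% |

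**Conservatism under restriction.** Simulation with 24 clusters and a normal covariate, keeping the best-balanced 30% of allocations on that covariate. The 30% is an assumption: the article gives only the roughly 10% that met all criteria jointly. True type I error of the unadjusted t-test at nominal 5% was 4.1%, 2.8% and 1.0% at ρ = 0.3, 0.5 and 0.7. With adjustment it lay between 4.6% and 5.4%. A looser restriction that kept 60% still gave 4.2%, 3.2% and 1.7% unadjusted.

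**Clusters without a pre-trial value.** The article does not say how many clusters have one. Suppose, for illustration, 18 of 24 did and the rest were dropped. Variance scales as (1 − ρ²)/n. At ρ = 0.5 that is 0.75/18 = 1/24, exactly the unadjusted 24-cluster variance, so nothing is gained and degrees of freedom are lost. At ρ = 0.3 it is 0.91/18, or 0.91×24/18 = 1.21 times the unadjusted variance. In power, with noncentrality 2.93×√(18/24)/√(1 − ρ²) on 15 degrees of freedom, 80% falls to about 70% at ρ = 0.3 and 78% at ρ = 0.5. Dropping clusters can therefore cost more than adjustment gains.

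**The case against.** The planned analysis is valid. A t-test on cluster summaries, with adjusted analyses beside it, is standard for 24 clusters, and a condensed article may leave further covariates to an analysis plan that is not shown. Validity is conceded. The second part does not dispose of the point, because the article does not leave the covariates open. It names a set for density, and a different, longer one for parity and sporozoite rate. The choice for density is stated and can be improved.

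The article says very little about the restriction value: not when or how it was measured, whether it was a count or a category, or in how many clusters. A reader might infer that a baseline of exactly the trial outcome, mosquitoes per trap per night, is on file for all 24 clusters. The document does not support that. It shows only that some cluster-level value entered the allocation. This objection stands, and it shapes the fix.

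The correlation and the starting powers are assumed. A different village or season would lower the correlation, and EIR also depends on the sporozoite rate, so its correlation with earlier density may be lower still. This stands too; at 0.3 the gain is modest.

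Year is not an idle covariate: 18 clusters were trapped in year 1 and 24 in year 2, so it has a purpose in pooled data. It still does not stand in for a cluster's earlier abundance.

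Finally, density and EIR are not the only vector evidence. The article uses parity as its measure of mosquito survival, and confidence intervals would make imprecision in density visible. It would go too far to say that a null result here must be read as no vector effect.

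**Conclusion.** The point holds as a minor improvement to a stated choice. A variable used to restrict the allocation, and likely to predict density and EIR, is missing from the analyses of both. The cost is imprecision and a somewhat conservative test.

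A reader might infer that the estimates are biased, or that the primary result is weakened. Neither follows: the unadjusted comparison remains unbiased under randomisation, and only secondary outcomes are touched.

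From an assumed 80% power the gain is about 3, 10 and 17 points at correlations of 0.3, 0.5 and 0.7. At zero correlation the loss is at most about 0.3 points. These figures assume a usable pre-trial value in every analysed cluster, a two-sided 5% test and a linear relation on the scale analysed. The size of the conservatism rests further on an assumed tightness of restriction.

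**What to change.** For mosquito density and EIR in secondary outcome 8, keep the planned t-test and present beside it a cluster-level regression of the summary on arm and the cluster's pre-trial vector density as used in the restriction, with inference from the t distribution on the residual degrees of freedom. Use the log scale for the summary where the plan already log-transforms it. Enter the covariate on the log scale if it is a count, or as categories if that is how it was held. State when, how and in how many clusters it was measured.

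Keep every analysed cluster. If any lacks a value, use a missing indicator or a value imputed without regard to arm, and do not drop clusters.

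The cost is a short addition to the analysis plan, specified before unblinding. The article's Trial status section places laboratory testing ahead of statistical analysis, so there was room for this. No new fieldwork is needed if the restriction value was retained. Statistically it costs one degree of freedom, or slightly more with a missing indicator or a multi-level category, and the gain shrinks as more clusters lack a value.

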
### Patient and public involvement

Qualitative studies report that this population almost unanimously consider malaria to be a significant problem in their homes and the region, that additional malaria control measures would be welcome, and that MDA is acceptable,^38 70^ all of which informed MATAMAL’s design.

All field assistants and the deputy trial manager are local residents and MDA will be delivered by ASCs within their own communities. Methods were finalised in discussion with these stakeholders, the Regional Health Directorate and MINSAP. There will be monthly feedback sessions with ASCs and staff during MDA and surveys. Trial outcomes, social science, public engagement and qualitative work will be presented to stakeholders and communities using plans developed with the contributors themselves.

### Trial status

All necessary approvals are in place. A baseline malaria prevalence survey was completed in November 2019. Two years of MDA has successfully been delivered across all clusters, alongside two annual cohort surveys and entomological sample collection. Two annual peak transmission surveys and a dry season NTD survey have been completed. Qualitative and social science work has taken place throughout. Laboratory testing is ongoing ahead of statistical analysis.

## Ethics and dissemination

MATAMAL will be reported according to CONSORT guidance.^71^ It is a collaboration between LSHTM, Medical Research Council The Gambia and MINSAP. Ethical approval has been obtained from LSHTM Research Ethics Committee (UK) (19156) and CNES (Guinea-Bissau) (084/CNES/INASA/2020), with additional regulatory approvals from The Gambia. Any changes to the protocol will be agreed by investigators and submitted to these same bodies for approval. The independent DSMB will oversee trial safety through annual meetings, advising the Trial Steering Committee on ongoing trial conduct. Members of these committees are listed in online supplemental material 9. Independent audit may be carried out by LSHTM, our funders or MRC The Gambia. This work abides by the Declaration of Helsinki^72^ and Good Clinical Practice.^73^

10.1136/bmjopen-2023-072347.supp9Supplementary data

Electronic forms are encrypted on submission to a LSHTM HERA-compliant secure server. Paper forms will be kept in limited-access locked storage at the site office. Data will be de-identified, except for consent and MDA record forms. All data will be held for a minimum of 7 years, including in LSHTM electronic repositories, whence access to de-identified data can be requested. All investigators will have access to cleaned databases.

Results will be published in peer-review journals, presented at conferences and to local collaborators. Field staff, nurses and ASCs will disseminate findings to participating communities in appropriate and accessible formats. Authorship will be decided on paper-by-paper basis, to recognise significant contributions to design, conduct, analysis and reporting. Writing will not be out-sourced.
